## Abstract

**Background:**

Physical inactivity and a sedentary lifestyle among community-dwelling older adults poses a greater risk for progressive physical and cognitive decline. Mixed reality technology-driven health enhancing physical activities such as the use of virtual coaches provide an emerging and promising solution to support healthy lifestyle, but the impact has not been clearly understood.

**Methods and analysis:**

An observational explanatory sequential mixed-method research design was conceptualized to examine the potential impact of a user-preferred mixed reality technology-driven health enhancing physical activity program directed toward purposively selected community-dwelling older adults in two senior centers in the Philippines. Quantitative components of the study will be done through a discreet choice experiment and a quasi-experimental study. A total of 128, or 64 older adults in each center, will be recruited via posters at community senior centers who will undergo additional screening or health records review by a certified gerontologist to ensure safety and proper fit. Treatments (live coaching with video-based exercise and mixed reality technology-driven exercise) will be assigned to each of the two senior center sites for the quasi-experiment. The participants from the experimental group shall be involved in the discreet choice experiment, modeling, and usability evaluations. Finally, a qualitative sample of participants (*n* = 6) as key informants shall be obtained from the experimental group using purposive selection.

**Discussion:**

This study protocol will examine the health impact of a promising mixed reality program in health promotion among older adults. The study utilizes a human-centered mixed method research design in technology development and evaluation in the context of developing nations.

**Clinical trial registration**: ClinicalTrials.gov, identifier NCT06136468.

## Introduction

Physical inactivity, is common among older adults, affecting one-third of the global population (1, 2), and accounts for an estimated $53.8 billion global economic burden on the healthcare system (3, 4). It is also responsible for around 10% of global deaths annually (4). In the United States alone, almost 80% of older adults are considered inactive (5). Recent literature reviews reported a radical change in older adults’ lifestyles during the COVID-19 pandemic that further reduced physical activity (6, 7). In the Philippines, a survey reports that 67% percent of older adults are inactive, further exacerbated by the current pandemic (8, 9). The limitation on physical activity progresses physical deterioration and development of comorbidities and is considered a decisive risk factor for all-cause mortality (10). As an exemplar, the odds of COVID-19 death are 2.49 higher for inactive and sedentary patients (11). Therefore, there is a solid call to promote exercise programs that foster physical activity engagement and reduce sedentary lifestyle in older adults, most especially in the post-pandemic era (8, 12) since older adults are particularly susceptible of leading inactive lifestyles (13).

Forms of health-enhancing physical activity (HEPA) (14) like structured physical exercise are essential factors in maintaining normal body function, healthy aging, and promoting a longer life span (15). Regular exercise can help reduce frailty, fall risk, and premature morbidity. It is also relevant in preventing and managing health conditions common in the older adult population, such as hypertension, diabetes, obesity, insomnia, depression, and anxiety. Multinational campaigns and guidelines recommend the most beneficial multimodal exercise programs consisting of aerobic, resistance training, flexibility, and balance components (16). However, despite the tremendous benefits of HEPA, such as physical exercise, studies show that older adults are not actively engaged in such heath activities. In addition to the lack of a structured and enticing program, scholars reported several socio-cognitive processes that impact exercise behavior, adoption, and maintenance (17). In support, scientists have long established the critical role of culture, society, and environment in the success of HEPA programs (18). This outcome reinforces the development of location and culture-specific country programs based on the cohort preferences and national policy to support older adults’ HEPA (13), which are currently few and still underdeveloped (19).

As healthcare institutes recommend HEPA initiatives as essential components of health promotion for older adults, tools, and technologies supporting active lifestyles are increasing in parallel. Population aging and technological diffusion are two intersecting transitions currently experienced by the world. More than ever, the increased aging of the population requires technology-driven nursing services (20) to complement the demand for quality health services, especially for older adults with declining health and physical and mental challenges (21, 22). For instance, the introduction of Fourth Industrial Revolution technologies for health promotion for older people represents an emerging and promising intervention (23). Furthermore, numerous HEPA activities geared towards balance and muscle strength can be performed at home or on-site using technology tools such as health trackers and gadgets (24). In addition, multiple online resources that feature virtual guides are emerging and available.

Emerging electronic health (eHealth) interventions have centered on behavioral change relating to physical activity. They have shown effectiveness in many instances (25). The latest innovations in technology-driven HEPA are the utilization of humanoid (human-resembling) technologies (HTs) like physical humanoid robot coaches (HRCs) (22, 26). Due to the advent of virtual worlds and mixed reality applications, virtual digital assistants as embodied conversational agents are also emerging (25). Digital “coaches” in exercise projected through mixed reality displays are particularly useful in situations where social contact might be limited, such as during the pandemic through remote coaching (27). In addition, companies are now investing in developing technologies whose main structure is the fusion of the virtual and physical world in a “metaverse” (28). Health experts have arrived at a consensus that the emergence of metaverse applications will provide a promising future in delivering healthcare in all “spaces” and “dimensions” (29). The emergence of virtual coaches and metaverse studies in nursing is still novice but growing with increasing acknowledgment of opportunities and challenges surrounding its implementation (30–32).

While mixed reality technology-driven health enhancing physical activities has been previously shown to reduce the risk of diseases (33, 34), studies focusing on its impact on physical and mental functioning among older adults are still limited and scarce (35, 36). Scholars also reported a substantial divide among users and non-users of technologies for physical health (37). Furthermore, technology-lead interventions have been previously reported to be potentially susceptible to disregard due to usability issues and task quality. As a result, current studies are recommended to focus on the development and evaluation of user-preferred technologies via mixed-method inquiry (25, 38) to understand better how older adults interact with the technology and leverage the technology to meet their needs (22).

## Objectives

In response to the current gray spots and gaps found in a recently published literature review (31), this study envisions to advance the science of mixed reality technology-driven health interventions in the field of nursing by examining its impact through an exercise program directed toward community-dwelling older adults. Specifically, it aims to:

*Quantitative aim 1*: to assess older adults’ preferences for an ideal mixed-reality-driven virtual coach program based on several attributes and levels. The subjects are hypothesized to select age and ability-specific choices based on previous exposure to technology and life experiences.*Quantitative aim 2*: to evaluate the impact of the mixed-reality-driven virtual coach program on participants’ health. The causal relationship between the outcome variables will be obtained from valid and reliable tools. Older adults with active participation in the program groups are hypothesized to elicit comparable physical and cognitive performances.*Quantitative aim 3*: to model the older adults’ perception of the mixed-reality-driven virtual coach program usability and predictors of intention to participate in the program. The subjects are postulated to show indications of higher behavioral intention to participate in the program as affected by various variables.*Qualitative aim 1*: to understand the older adult participants’ experiences during the mixed-reality-driven virtual coach program. A narrative descriptive qualitative approach will be carried out to evaluate the challenges or difficulties and successes or benefits of the program among those who benefitted the least and most from the intervention. The older adult key informants are expected to story-tell their practices focusing on themes related to acceptability, barriers, and facilitators.

Overall, tt was hypothesized that: (a) the older adult participants will identify their technology preferences based on their previous experiences and combination of various attributes, and (b) the use of mixed reality technology in physical exercise program will produce comparable health assessments when compared with the traditional form of health enhancing physical activities.

Human-computer interaction (HCI) is core to ensuring the usability of technologies and their successful integration to practice (39–42). Previous literature (43, 44) highlighted that HCI directly impacts technology users’ behavioral intention and actual utilization (44). Therefore, the adapted HCI model (45) offers a robust framework for the study. This model highlights a multitude of essential factors that needs to be considered in technology adoption such as content (user-preference), computer (technology features) and context (individual experiences and client uniqueness) that serves as antecedents of successful technology use in healthcare.

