### Sample size

To identify the acceptable sample size, the difference in repeated measures between two independent groups using MANOVA with a power set at 0.80 with medium to high effect size at 0.05 alpha level was computed using R software. The estimated sample size is 128 or 64 participants per senior center group.

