### Comparing the effects of the mixed reality technology-driven health enhancing physical activities with the usual health enhancing physical activities (live coach and video-based) on participants’ physical, cognitive status, and quality of life measures

#### Repeated measures analysis of variance (RM-ANOVA)

Repeated Measures Analysis of Variance (RM-ANOVA) will be used to investigate the effects of the type of intervention on health variables across three assessment points using SPSS version 22. Mauchly’s Test will be utilized to verify the sphericity assumption with degrees of freedom correction using the Greenhouse–Geisser method. Effect sizes will also be reported.

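### The health hypothesis is comparability, but the planned analysis and the sample size are both for detecting a difference, with no margin

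*Protocol article*

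**What the plan says.** The Objectives section of the protocol article states the health hypothesis twice. Quantitative aim 2 reads: "Older adults with active participation in the program groups are hypothesized to elicit comparable physical and cognitive performances". Overall hypothesis (b) names the comparator and says that the mixed-reality programme "will produce comparable health assessments when compared with the traditional form of health enhancing physical activities".

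The section on repeated measures analysis of variance gives the only between-programme analysis. RM-ANOVA "will be used to investigate the effects of the type of intervention on health variables across three assessment points using SPSS version 22", with a sphericity check and a Greenhouse–Geisser correction. It adds: "Effect sizes will also be reported".

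The Sample size section bases the calculation on "the difference in repeated measures between two independent groups using MANOVA". Its settings are given as "a power set at 0.80 with medium to high effect size at 0.05 alpha level", and it arrives at 128 participants, 64 per centre.

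The article gives no equivalence or non-inferiority margin, no rule comparing a confidence interval with a margin, and no numerical meaning for comparable. It does not say how a non-significant result will be interpreted.

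**The concern.** A prediction of similarity against a named comparator is an equivalence-type hypothesis. RM-ANOVA takes no difference as its null, so a significant programme effect (main effect or programme-by-time interaction) would count against the hypothesis, and only failure to reject could be taken as support. Failure to reject becomes more likely as the study gets smaller, loses more participants or measures less precisely, so weaknesses in conduct would favour the predicted conclusion.

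This is not a detail left for a statistical analysis plan. The article itself fixes the hypothesis, the test and the basis of the sample size, and the three do not match. The margin also decides whether 128 is enough, so it has to be settled together with the sample size and before data are seen.

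**Working it through.** **Inputs.** From the article: 64 per group, power 0.80, alpha 0.05, an effect described only as medium to high, three assessment points. Assumed here: a two-sided test, a medium effect of d = 0.5, all margins, a baseline-to-follow-up correlation of 0.6, a correlation of 0.5 between two post-baseline values, between-outcome correlations of 0 to 0.5, and no loss unless stated.

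**1. The plan's own figure.** A two-sided two-sample t-test at d = 0.5 with power 0.80 needs 63.8, so 64 per group and 128 in total; power at 64 is 0.801. The stated 128 is therefore what a plain difference test at a medium effect requires.

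**2. Chance of a non-significant result when a difference exists.** Take one value per person and 64 per group. The standard error in SD units is sqrt(2/64) = 0.177, the noncentrality is d/0.177 and the critical value is t(0.975, 126) = 1.979.

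| True difference | One value per person | Mean of two post values |
|---|---|---|
| 0.3 SD | 61% | 51% |
| 0.4 SD | 39% | 26% |
| 0.5 SD | 20% | 10% |

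The last column uses the variance of a mean of two values, (1 + 0.5)/2 = 0.75, so the SD is 0.866 and the effective differences are 0.3/0.866 = 0.346, 0.4/0.866 = 0.462 and 0.5/0.866 = 0.577.

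The single-value 95% interval has half-width 1.96 × 0.177 = 0.35 SD. An estimate just short of significance therefore has an interval reaching to about 0.7 SD.

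**3. What 128 gives for a comparability test.** Use two one-sided 5% tests, which is the same as a 90% interval lying inside ±m, with true difference 0. In the normal approximation, power = 2Φ(m/0.177 − 1.645) − 1.

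- m = 0.5 SD: 2Φ(2.828 − 1.645) − 1 = 0.763 (0.76 with t quantiles)
- m = 0.4 SD: 2Φ(2.263 − 1.645) − 1 = 0.463 (0.46 with t)
- m = 0.3 SD: 2Φ(1.697 − 1.645) − 1 = 0.042 (0.05 with t)

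Baseline adjustment with r = 0.6 multiplies the SD by sqrt(1 − 0.36) = 0.8. A 0.5 SD margin then acts as 0.5/0.8 = 0.625 (power 0.94), and a 0.4 SD margin as 0.4/0.8 = 0.5 (power 0.76).

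**4. If 6-minute walk, MoCA and SF-8 must all pass.** With independent outcomes the joint power is the cube of the single-outcome power. The upper figures are simulated with a between-outcome correlation of 0.5.

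| Margin | Unadjusted | Adjusted, r = 0.6 |
|---|---|---|
| 0.5 SD | 0.759³ = 0.44, up to 0.49 | 0.939³ = 0.83, up to 0.85 |
| 0.4 SD | 0.456³ = 0.09, up to 0.12 | 0.44 to 0.49 |

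The stated 0.80 therefore does not carry over to comparability. It depends on the margin, the adjustment and whether one or three outcomes must pass.

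**The case against.** The strongest reply is that comparable is a loose expectation and the study is really one of estimation. Aim 2 sets out to evaluate impact, the Design section speaks of comparing effects, the quasi-experiment section speaks of estimating the effect, and effect sizes will be reported. That reading is possible. It does not remove the mismatch, because the article states no other hypothesis about the health difference between programmes. It does mean that rewording the hypothesis is a legitimate repair, and it is offered below. An effect size without an interval judged against a margin does not test comparability.

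A second reply is that the 61%, 39% and 20% describe one observation per person, whereas the plan uses three assessment points. That stands. Those figures are an illustration, and repeated values lower them, as the table shows. The problem shrinks but remains at 0.3 and 0.4 SD.

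Two stronger readings are tempting, and the document supports neither. A reader might infer that the investigators will present a non-significant result as proof of comparability; the article gives no interpretation rule, so this cannot be attributed to them. A reader might also infer that a clearly worse programme would often pass as comparable. On the single-value basis, non-significance falls to 8% at 0.6 SD and 0.6% at 0.8 SD, so often applies only to differences of about 0.3 to 0.4 SD. Nor is comparability named as the main hypothesis: it is one half of a two-part overall statement within four aims.

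**Conclusion.** The mismatch is real and rests on the article's own text: a comparability hypothesis, a difference test, a sample size for a difference, and no margin. Followed as written, the plan can support its health hypothesis only by failing to reject, and with 64 per group that is a common outcome at true differences of 0.3 to 0.4 SD (61% and 39% on one value per person; about 51% and 26% on the mean of two).

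The textual conclusion needs no assumption. Its size rests on the assumed margins, correlations, sidedness and absence of loss listed with the inputs. It needs correcting before data collection, and it can be corrected without enrolling more participants, provided the resulting power is stated honestly.

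**What to change.** Choose one of two routes before data collection.

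1. **Keep the comparability hypothesis.** State a margin, in units of the measure, for each of 6-minute walk, MoCA and SF-8 at a named assessment point. Claim comparability for an outcome only if the 90% confidence interval of the baseline-adjusted between-group difference lies wholly inside its margin. Say whether the claim is per outcome or requires all three; an all-must-pass rule needs no alpha adjustment. Restate power at 128 for that rule, using the joint figures if all three must pass.
2. **Reword the hypothesis** as a question of difference or estimation, and report between-group differences with confidence intervals.

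Under either route, add a sentence that a non-significant RM-ANOVA will not be taken as comparability.

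The cost is wording and, for the first route, agreement on three margins. The stated power becomes margin-dependent and less favourable. A joint power above 0.80 at 128 holds only for a wide margin (0.5 SD), useful baseline adjustment and little loss: with an assumed 20% loss (51 per group) it falls from 0.83–0.85 to about 0.64–0.69.

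Neither route cures the assignment of one centre to each programme (Study setting, subject, and eligibility criteria). An interval inside the margin could still reflect offsetting centre effects, and the conclusion should be limited accordingly.

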## Methods

### Design

An explanatory sequential mixed-method research design will be used to understand the impact of the mixed-reality-driven virtual coach program community-dwelling Filipino older adults and compare its effects against the current exercise program (live coaching and video-based) on the participants’ health. The current study advances four (4) research phases that will make use of distinct research approaches. Phases 1–3 shall adopt a post-positivist approach (46) through discreet choice experiment (conjoint analysis), quasi experiment, and structural equation modeling. Phase 4 follows a qualitative-constructivist paradigm (47) using descriptive qualitative research.

#### Phase 1: older adults’ preference for an ideal mixed-reality-driven virtual coach program

##### Discrete choice experiment

Understanding how older adults value the essential components of healthcare interventions through the conjoint method is crucial to both the design and evaluation of the program (48). Discrete choice experiment (DCE) or conjoint analysis involves measuring psychological judgment between choices and alternatives. It is also powerful in understanding and predicting the technology users’ attribute tradeoffs, decisions, and preferences of technology features (49). DCE was initially introduced in psychology and marketing but has gained popularity in medicine and healthcare (50). The adaptive conjoint analysis method is the most appropriate for the current study due to its practical and respondent-friendly features (51). This study will follow the published standards in applying the conjoint analysis methods in healthcare (52). In addition, it will include essential steps in the development of the adaptive conjoint survey, as follows: (a) defining HT-HEPA attributes and levels based on literature evidence, and (b) designing the attributes and levels as components of the HT-HEPA program, and (c) designing the conjoint survey questionnaire. The computer-based survey questionnaire using the Sawtooth software will be distributed to participants.

#### Phase 2: impact of mixed-reality-driven virtual coach program on participants’ physical, cognitive status, and QoL

##### Quasi experiment

Quasi experimental research will be employed to estimate the effect and examine the causal relationship between the HT-HEPA intervention and the study respondents’ physical, cognitive status, and QoL. Quasi experiments are appropriate for practical situations and ethical compliance for studies involving vulnerable participants such as older adults (53), and allow scholars to conduct rigorous studies under certain limitations and non-control conditions (54).

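### Phase 2 is worded as measuring the health impact of the mixed-reality programme, but with an exercise programme as the only comparator it can address at most the difference between the two

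*Protocol article*

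**What the plan says.** The protocol article puts two different questions to Phase 2.

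- **Absolute.** Quantitative aim 2 (Objectives) is "to evaluate the impact of the mixed-reality-driven virtual coach program on participants" and their health. The Phase 2 heading also speaks of impact, and the Quasi experiment section says the study will "estimate the effect and examine the causal relationship between the HT-HEPA intervention and the study respondents", with physical status, cognitive status and quality of life as outcomes.
- **Relative.** The Design section starts from understanding the impact and then adds that the study will "compare its effects against the current exercise program (live coaching and video-based"). Overall hypothesis (b) is that mixed reality "will produce comparable health assessments when compared with the traditional form of health enhancing physical activities". The analysis section on repeated measures ANOVA will "investigate the effects of the type of intervention on health variables across three assessment points", under a heading that compares the programme with the usual activities.

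The expected answer is the same under both. Aim 2 itself says that the groups "are hypothesized to elicit comparable physical and cognitive performances".

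The arms are described in the Abstract: "Treatments (live coaching with video-based exercise and mixed reality technology-driven exercise) will be assigned to each of the two senior center sites". Both arms exercise, and each treatment goes to one whole centre. No unexposed, wait-list or usual-activity group is described.

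**The concern.** A two-arm comparison identifies the difference between the two arms. With an active exercise programme as the other arm, that difference is the effect of one delivery method over another. It says nothing about how either compares with no programme. Aim 2 and the Quasi experiment section ask the latter question, and no contrast in the design answers it.

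The hypothesis makes this more than a matter of style. A comparable result would support a health impact only if live/video coaching is itself known to improve these outcomes over one month in this population. The Introduction cites general benefits of regular exercise, but the article gives no such evidence for this comparator, these outcomes and this duration, and does not make it a condition of the conclusion. Two effective programmes and two ineffective ones would both look comparable.

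At stake is what the trial may conclude on its main health question.

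**Working it through.** **Inputs from the protocol article.** 128 participants, 64 per centre; alpha 0.05; power 0.80; a medium to high effect size with no number (Sample size). Repeated measures ANOVA over three assessment points (statistical methods). Three outcome domains: physical, cognitive, quality of life.

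**Assumptions.** Two-sided testing, d = 0.5, the correlations, the retest gain and the margin used below. The article gives none of these.

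**1. The plan's own figure.** A two-sided two-sample t-test at alpha 0.05 with d = 0.5 and power 0.80 needs 64 per arm, 128 in total (exact power 0.801). The stated size is thus reproduced by a test of the difference between two groups.

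**2. Does a comparable result separate the two situations?** When the true change is the same in both arms, the group-by-time test is non-significant with probability 1 − 0.05 = 0.95 per outcome. This holds whether the common change is zero or positive. A simulation of the repeated measures ANOVA (20,000 runs, 64 per arm, three time points, correlation 0.5) gave:

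| True situation | Group-by-time non-significant |
|---|---|
| Neither programme has any effect | 94.7% |
| Both improve health by 0.25 SD | 94.9% |

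The two situations cannot be told apart. For all three outcomes together, if independent, the probability is 0.95³ = 0.857.

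**3. Would an equivalence-type test cure it?** No. With 64 per arm the standard error of the difference is √(2/64) = 0.177 SD. With two inert programmes and an assumed non-inferiority margin of 0.5 SD, the margin is met with probability Φ(0.5/0.177 − 1.96) = Φ(0.87) = 0.81. This point is therefore separate from the choice between a difference test and an equivalence test.

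**4. Can change over time fill the gap?** Suppose neither programme works but retesting alone adds d SD in both arms. For a paired test with correlation r, the noncentrality is d/√(2(1 − r)) × √n. With d = 0.25, r = 0.50 and n = 128 it is 0.25/1 × 11.31 = 2.83, and the time effect is significant with probability 0.80. With d = 0.10 the noncentrality is 1.13 and the probability 0.20. Within the mixed-reality arm alone (n = 64, d = 0.25) the noncentrality is 2.00 and the probability 0.50. In the three-point simulation above, a 0.25 SD shift in both arms gave a significant time effect in 1 − 0.163 = 0.837 of runs. The test gives the same answer whether the shift is benefit or retest gain.

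**5. How clean is the relative contrast?** Treatment and centre coincide. If neither programme works but the centres' trends differ by an assumed 0.2 SD, then with two time points and r = 0.50 the noncentrality is 0.2/1 × √(64/2) = 1.13. Non-significance falls from 0.95 to 0.80, and the significant results would reflect centre, not programme.

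**The case against.** The strongest reply is that the relative question is already there. The Design section, hypothesis (b) and the analysis section all pose a comparison with the usual programme, an active control is a legitimate choice, and the word effect in the Quasi experiment section can be read as effect against that control. All of this stands. It confines the fault to the impact and causal wording in Aim 2, Design and Quasi experiment, but does not remove it: those passages are not limited to a comparison, and Design asks for the impact in addition to the comparison.

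The 0.95 is simply 1 minus alpha. It is per outcome and assumes no site-by-time difference. The retest gain is assumed too. Table 2 cites reliability between versions of the MoCA, so alternate forms may be intended, which could reduce learning on that test. The figures illustrate the problem and do not predict the trial's results.

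A reader might infer three stronger things that the documents do not support:

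- **That the plan will report a comparable result, or improvement over time, as benefit.** No section says so. It is a risk that the wording leaves open. A flat time effect would also usually be visible: with no change in either arm, it was non-significant in 94.7% of simulated runs.
- **That the programme is too small to work, because its weekly dancing time is below the 150 minutes listed in Table 1.** The same row lists 20–60 minutes per session, 2–7 times per week, and the programme has other components. Falling below one listed figure is not evidence of no effect.
- **That the Step 1 health screening could serve as a pre-programme measurement of retest and time trends.** It is described as a health check, not an outcome assessment.

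**Conclusion.** The concern holds as a mismatch between the stated objective and what the design can identify. The absolute impact, or causal effect, named in Aim 2, Design and Quasi experiment has no identifying contrast. The hypothesised comparable result is reached with about the same probability, 0.95 per outcome, whether both programmes work equally or neither does. That figure assumes equal centre trends. Within-arm change is not a substitute: under an assumed 0.25 SD retest gain and a correlation of 0.50, it would be significant with probability 0.80 with no benefit at all.

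This is not a case against the active control, nor a finding that the programmes are ineffective. It would also be wrong to infer that the group-by-time contrast is sound once the objective is made relative. With one centre per treatment it remains a comparison of two centres, and is not cleanly causal.

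**What to change.** 1. Reword Quantitative aim 2, Design and the Quasi experiment section so that the Phase 2 objective is the difference between the mixed-reality programme and live/video coaching in physical status, cognitive status and quality of life. This matches hypothesis (b) and the analysis section. Remove the absolute impact and causal-relationship wording.
2. In the repeated measures ANOVA section, state that time effects and within-arm changes are descriptive and not evidence of benefit, and that the group-by-time contrast compares one centre with another and so cannot be read as a clean causal effect of the programme.
3. State that a comparable result will not be reported as showing a health benefit of either programme.

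These are wording changes. They need no extra participants, visits or arm. The cost is a narrower conclusion than health impact.
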